## Abstract

**Background:**

End-stage kidney disease (ESKD) or kidney failure is a condition where the kidneys lose the ability to function. African American individuals are 4 times as likely to develop ESKD compared to White American individuals. In addition, African American patients are less likely to have an optimal dialysis start and to choose renal replacement therapy modalities that align with their goals and values. Our prior work shows that culturally tailored, in-person education improves patient outcomes. This is the foundation for our innovative intervention using an African American virtual patient educator as an option for hospitalized patients with chronic kidney disease (CKD).

**Objective:**

The Interactive Computer-Adaptive Chronic Kidney Disease (I-C-CKD) study will determine whether the computerized adaptive education and usual hospital care impact the health literacy of African American patients with kidney disease. It will also assess how patients’ lifestyle and commitment to health goals are impacted by the method of health literacy education.

**Methods:**

We will screen, recruit, and enroll hospitalized patients who self-identify as African American and have advanced CKD based on their estimated glomerular filtration rate. Eligible patients who verbally consented will be randomly assigned into either the computerized adaptive education intervention group or the control group (usual hospital care). Patients in the intervention group will receive a culturally tailored, adaptive education module. To analyze pretest, posttest, and follow-up survey results on patient CKD knowledge, ESKD treatment options, and health goals, we will use a paired, 2-tailed *t* test with a Bonferroni adjustment for multiple comparisons.

**Results:**

Recruitment for the I-C-CKD study began on May 2, 2023. We are currently recruiting and have enrolled 96 patients who completed both pretest and posttest surveys as of December 2024. This includes 50 patients in the control group and 46 patients in the intervention group. Data analysis has not occurred.

**Conclusions:**

African American individuals often receive less patient education about self-care and treatment options for CKD. We hope this study provides a solution to increase hospitalized African American patients’ knowledge of CKD and motivation for CKD self-care through computerized adaptive education, reduce disparities, and improve patient outcomes.

**Trial Registration:**

ClinicalTrials.gov NCT06364358; https://clinicaltrials.gov/study/NCT06364358

**International Registered Report Identifier (IRRID):**

DERR1-10.2196/66846

## Introduction

### Background

End-stage kidney disease (ESKD) or kidney failure is a condition where the kidneys lose the ability to function. African American individuals are 4 times as likely to have ESKD compared to White American individuals [1]. African American patients are more likely to have comorbidities such as diabetes, obesity, high blood pressure (hypertension), and heart failure, which all increase the risk of developing kidney disease [1].

Hemodialysis can help patients with ESKD feel better and live longer. However, dialysis is not a cure for ESKD, and patients on hemodialysis have high morbidity and mortality rates [1]. Patients on hemodialysis can also experience side effects such as low blood pressure (hypotension), muscle cramps, sleep problems, anemia, bone disease, high blood pressure (hypertension), and access-site complications [2]. In-center hemodialysis (IHD) with thrice weekly sessions in a dialysis unit is the most common treatment for ESKD. Patients who use IHD experience greater inconvenience, worse waste clearance, and more issues with transportation in comparison to other ESKD options. Alternatives to IHD include home hemodialysis, peritoneal dialysis, and kidney transplantation. These methods are associated reduced morbidity and mortality, or improved quality of life, compared to IHD [3].

There are racial disparities in the use of these renal replacement therapy (RRT) modalities. African American patients are less likely to be informed about better RRT options. African American patients are 47% less likely to use peritoneal dialysis and 3.5 times less likely to have a kidney transplant [4]. Often, African American patients are less likely to receive information from their provider about their CKD stage, treatment options, and self-care to prevent and treat CKD [3]. The hospital can be an important intervention site because hospitalization rate rises sharply in the 3 months before dialysis initiation. In addition, even patients who are not connected to primary or specialty care can present to the hospital.

Our previous work to was to develop and test a hospital-based CKD intervention, PREP RRT (Patient Referral and Education Program Prior to Renal Replacement Therapy). To develop the intervention, we interviewed African American patients about CKD knowledge and barriers to RRT preparation [4,5]. The intervention in that study includes an in-person African American health educator and written materials [2]. Our results showed an increase in knowledge in the intervention group compared to control group. We also found that culturally tailored interventions improved patient outcomes [6]. Drawing from insights gained in our prior work, our research team developed and implemented the Interactive Computer-Adaptive Chronic Kidney Disease (I-C-CKD) education as a patient education intervention to inform hospitalized African American patients with advanced CKD about their CKD and RRT options. This computer-based education is predicted be more accessible for hospitalized patients through videos that are culturally tailored with a virtual African American narrator, as in-person educators have some limitations.

### Primary Hypothesis

Our primary hypothesis is that the computerized adaptive education will be more effective than usual hospital care in improving knowledge about CKD, CKD self-care, and RRT options (primary outcome).

### Secondary Hypothesis

Our secondary hypothesis is that the computerized adaptive education will increase patients’ intent to participate in CKD self-care compared to usual hospital care. We also believe that the computerized adaptive education will increase patients’ action and commitment to CKD health-seeking behavior, access planning prior to dialysis initiation, initiate home dialysis modalities, and/or have a transplant evaluation after discharge and beyond 30-day follow-up.

## Methods

### Trial Design

The I-C-CKD study is a hospital-based, randomized controlled trial of a computerized patient education intervention compared to usual hospital care. After obtaining verbal consent (Multimedia Appendix 1), each patient will be randomly assigned into two groups: usual hospital care (control group) and the computerized adaptive education (intervention group), which is assisted by a research assistant (RA).

The usual hospital care control group will feature a baseline General Health Knowledge and Intent survey. Participants in the usual hospital care control group will receive the pretest survey and education materials but will not receive specific knowledge about CKD or their CKD condition. Participants in the control group will receive printed patient education materials informing them of the importance of a general healthy lifestyle, including diet, physical activity, and medication adherence. The printed materials for the usual hospital care control group are meant for patients with cardiovascular conditions and do not have any information about CKD. Participants who receive the control condition will also be able to speak with the patient educator if they want to.

The computerized adaptive education intervention group will receive the advanced CKD education module with information on the risk factors, stages, treatment options, and lifestyle of patients with CKD (see Figures 1 and 2). The RAs will assist with the program but not offer any information or knowledge about CKD. Following the patient’s review of the advanced CKD education module, the RAs will administer the posttest General Health Knowledge and Intent survey.

**Figure 1 figure1:**
[figure not shown]
Screenshot of the computerized adaptive education intervention featuring a personal story.

**Figure 2 figure2:**
[figure not shown]
Screenshot of the computerized adaptive education intervention regarding treatment options. CKD: chronic kidney disease.

Both the usual hospital care control group and the computerized adaptive education intervention group will complete the “What’s Next” form, to assess the patient’s commitment to specific self-care activities. Patients will select their top-3 health goals, rate how confident they are about each goal, and identify how important each goal is to them. Patients will also report on their health resources. All the forms will be sent to the patient educator, a trained nephrology social worker.

Each patient will be contacted 30 days after discharge to ask about their commitment to health goals, barriers to self-care, and treatment plans.

The SPIRIT (Standard Protocol Items: Recommendations for Interventional Trials) checklist is provided in Multimedia Appendix 2.

### Participants and Eligibility

The study will take place at the University of Chicago Medical Center (UCMC). We will approach hospitalized, English-speaking, African American patients at UCMC, aged 18-70 years, who meet the criteria for advanced CKD (Stage 3b or greater) with an estimated glomerular filtration rate (eGFR) <45 mL/min/1.73 m^2^; they must not be on dialysis yet or have a history of kidney transplant. In order to be eligible, patients must have an eGFR <45 mL/min/1.73 m^2^ during the current hospitalization in addition to prior hospitalizations and/or outpatient visits. We will have access to prior UCMC inpatient and outpatient laboratory values. We will also have access to some inpatient and outpatient laboratory values from other medical centers through Epic Care Everywhere. The exclusion criteria include patients who are hospitalized in the intensive care unit, meet the Montreal Cognitive Assessment criterion for cognitive impairment, or require a proxy for study consent. We will enroll 170 participants and randomly assign 85 to the computerized adaptive education and 85 to usual hospital care.

### Recruitment

This study will be a substudy of the Hospitalist Project, an ongoing clinical study that examines a variety of outcomes of patients hospitalized in our general internal medicine services, and includes the analysis of administrative data, inpatient interviews, and 30-day follow-up by phone [7]. Hospitalist Project staff will obtain basic demographic information and medical history. Per the Hospitalist Project protocol, staff will also obtain permission to contact patients after discharge and to access their medical records (ie, at UCMC, from other medical systems, and through Medicare linkage). All inpatients recruited to the Hospitalist Project will be screened daily by the RA to identify patient eligibility for the study.

We will approach all Hospitalist Project–enrolled patients who meet study criteria and obtain informed verbal consent.

### Randomization

Participants will be randomly assigned using a computerized spreadsheet, assigning each participant a random number. Participants who are assigned an odd number will be assigned to the intervention group. Participants who are assigned an even number will be assigned to the control group. The RA will begin by identifying an eligible participant who consented to the Hospitalist Project. Then, they will use the randomization spreadsheet to determine if the participant will be part of the intervention group or the control group. They will then approach the patient with the appropriate form and study packet.

The RA will complete the randomization, assignment, and enrollment process.

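### The Randomization section reveals the patient's group before trial consent and pretest, whereas the Abstract and Trial Design place randomisation after consent

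*Protocol article*

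**What the plan says.** Two orders of events stand in the protocol article.

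- **Consent, then randomisation.** Trial Design: "After obtaining verbal consent (Multimedia Appendix 1), each patient will be randomly assigned into two groups". The Abstract (Methods) agrees: "Eligible patients who verbally consented will be randomly assigned into either the computerized adaptive education intervention group or the control group".
- **Randomisation, then approach.** The Randomization section begins: "The RA will begin by identifying an eligible participant who consented to the Hospitalist Project". It goes on: "Then, they will use the randomization spreadsheet to determine if the participant will be part of the intervention group or the control group". Then: "They will then approach the patient with the appropriate form and study packet".

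Consent to this trial is not the parent-study consent. Ethical Considerations describes written consent for the Hospitalist Project and a further verbal consent for I-C-CKD. Recruitment ties the verbal consent to the approach: "We will approach all Hospitalist Project–enrolled patients who meet study criteria and obtain informed verbal consent".

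On roles, the Randomization section says: "The RA will complete the randomization, assignment, and enrollment process". Blinding states that the research team is unblinded. The Intervention Group and Control Group sections have the RA conduct the pretest in both groups. Under Primary Outcome, the measure is change from that baseline.

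**The concern.** Randomisation protects a comparison only if neither entry to the trial nor the baseline measurement can be influenced by the group. Under the Randomization order, the RA role holds the current patient's group, and the matching packet, before asking for consent. Three things can then depend on the group: how strongly the patient is encouraged to take part, who refuses, and how the pretest is given. A refusal at that point is a loss after randomisation, and such losses can differ by group. A shift in pretest scores enters the primary outcome directly, because the outcome is a difference from the pretest.

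**Working it through.** **1. The plan's own figure.** Inputs from Statistical Methods: difference 10, SD 21, one-sided 5%, power above 90%, 77 per group. Normal approximation: n = 2 × 21² × (1.645 + 1.282)² / 10² = 75.5, so 76 per group. The noncentral t gives 77, with 90.3% power. The stated 77 is reproduced, and this point does not dispute it.

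**2. The order of steps.**

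| Step | Abstract and Trial Design | Randomization, with Recruitment |
|---|---|---|
| First | Verbal consent to this trial | Eligible patient with parent-study consent identified |
| Second | Random assignment | Group looked up in the spreadsheet |
| Third | Group procedures, including pretest | Patient approached with group packet; trial consent sought |
| Fourth | – | Pretest conducted by the RA |

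Could the two-stage consent reconcile the columns? Only if consent in the Abstract and Trial Design meant the parent-study consent. It does not: both say verbal, and Ethical Considerations makes the parent consent written and the trial consent verbal. The only consent that the Randomization section names before the lookup is the parent one. The conflict stands.

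**3. The pretest.** No section places the pretest before allocation. The Intervention Group and Control Group sections each describe it as part of that group's procedures. Aligning the text to consent-then-randomise would therefore protect consent but not the baseline measurement.

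**4. How a bias would enter a change score.** Let f and g be the refusal proportions in the two groups, and d the gap in mean *change* between those who accept and those who refuse, taken as equal in both groups. The spurious difference is (f − g) × d.

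- Refusers score 10 points lower at both pretest and posttest: d = 0, so the bias in change is 0.
- Assumed d = 10 and f − g = 0.10: 0.10 × 10 = 1 point.
- Assumed d = 10 and f − g = 0.20: 0.20 × 10 = 2 points.

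A group-dependent shift in the pretest needs no such product. A pretest mean 2 points lower in one group, with the posttest unaffected, moves the difference in change by 2 points.

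**5. What such a shift does to the error rate.** SE of the difference = 21 × √(2/77) = 3.38 points, taking the plan's SD as that of the analysed change. With no true effect and a bias of b points towards the intervention, the one-sided rejection probability is 1 − Φ(1.645 − b/3.38). The two-sided figure uses 1.96 and both tails.

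| Assumed b (points of change) | One-sided 5% becomes | Two-sided 5% becomes |
|---|---|---|
| 1 | 8.9% | 6.0% |
| 2 | 14.6% | 9.1% |
| 3 | 22.4% | 14.4% |

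Every b is an assumption; the document gives nothing from which to estimate it.

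**6. What the enrolment count can show.** Results reports 50 control and 46 intervention patients. Under simple 1:1 allocation the two-sided binomial p is about 0.76. The count covers only patients who completed both surveys, so it neither shows nor excludes differential refusal.

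**The case against.** The strongest reply is that the Randomization section may be loosely worded, and that an article leaves access controls to the full protocol. The second part is fair: a missing concealment paragraph would be no finding. But the article does state an order, and that order contradicts two of its other sections. If the wording is loose, it still needs correcting.

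Several stronger readings are tempting and are not supported:

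- *The list is open and the RA can see ahead.* The text describes a computerised spreadsheet giving each participant a random number. That fits numbers generated one at a time as well as a visible list. The point does not need this, since the current patient's group is known before the approach either way.
- *The RA chooses whom to approach by group.* The stated rule in Recruitment is to approach every eligible patient, with no discretion granted. What remains is how the approach is made.
- *One person does everything.* The RA is a role, and Trial Design uses the plural.
- *Control patients face only a leaflet while intervention patients face a 30-45 minute module.* The Control Group section also mentions a general health video module, of unstated length, so the difference in burden is unclear. Participants are not told their group, which limits refusal driven by patients' own knowledge of it. What they hear about session length is in the consent appendix, which is not shown.
- *Refusers with lower scores bias the result by that gap times the difference in refusal.* That holds for score levels. A constant gap cancels in a change score, and only a gap in gain matters. If the intervention has no effect, gains may be small for everyone, so large gaps in gain are less plausible.

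The pretest is viewed as a Google Form with multiple-choice and Likert items. This narrows the RA's influence but does not remove it, because the RA is said to conduct the pretest in both groups.

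**Conclusion.** The point holds as a contradiction with a real consequence. The Randomization section cannot be reconciled with the Abstract and Trial Design. Followed as written, it gives an unblinded RA role the group before consent and before the measurement that anchors the primary outcome.

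A reader might go further and infer that the patients already enrolled are a biased sample. The documents do not support that: they show exposure, not occurrence, and contain no refusal data. The size is therefore conditional. On the plan's SD and 77 per group, a spurious difference in change of 1 to 3 points, well below the target of 10, would roughly double to quadruple a one-sided 5% error.

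**What to change.** Bring the Abstract, Trial Design and Randomization sections to one order: confirm eligibility; obtain verbal consent to this trial; complete and save the pretest; then reveal that patient's allocation. State that the allocation is not visible to the recruiting RA until the pretest is saved, for example through automated release of one record at a time.

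For patients already enrolled, report the numbers assigned, refused and completed by group, as far as they were recorded, and say so where they were not. Optionally add a sensitivity analysis by period before and after the change.

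The cost is a short amendment and a one-time set-up of the release mechanism. There is no extra visit, and the sample size is unaffected. With 96 completers against a target of 170 at the last count, and recruitment then still open, later enrolments can still be protected.

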### Blinding

Trial participants will be blinded after group assignment. Participants will view the survey as a Google Form and will not be informed whether they are part of the intervention or control group. They will also receive a study packet, which will not identify if they are part of the intervention or control group. The research team will not be blinded.

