### Intervention Group

The RA will meet each participant and conduct the pretest survey in the participant’s private hospital room. The computerized adaptive education intervention group will receive an advanced CKD education module with information about CKD risk factors, stages, treatment options, and lifestyle modifications. The RA will assist in advancing program modules but not offer any information or knowledge about CKD. The avatar will be an African American woman who will present statistics about African American individuals and CKD. The interactive component will allow participants to personalize the information received based on prior CKD knowledge, diabetes status, and the level of motivation. The interactive CKD video can be completed in 30-45 minutes. Following the patient’s completion of the advanced CKD education module, the RA will then readminister the General Health Knowledge and Intent survey.

The computerized adaptive education intervention group (and the usual health care control group) will complete the “What’s Next” form, to assess the patient’s commitment to specific self-care activities. Patients will select 3 health goals from a list of 10 options, rate their level of confidence in the ability to make change, and identify an action plan to accomplish each goal. Moreover, patients will be asked to report their needs from the medical care team and for community assistance, and they will be provided a resource list. The study will also ask if patients would like a primary care doctor and/or a nephrologist. This information will be relayed to the primary inpatient team. All the forms will be sent to the patient educator, a trained nephrology social worker.

We will encourage participants to complete the voluntary study in one visit. At 30 days after discharge, both groups will complete a follow-up call with the project RA. Participants will be queried about progress on goals set on the health commitment form, knowledge, and health intent.

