### Control Group

The RA will meet each patient and conduct the pretest survey in the participant’s private hospital room. The usual hospital care control group will receive the General Health Knowledge and Intent pretest survey and printed education materials without explicit CKD information or knowledge about their CKD condition. The distributed education materials were intended for patients with cardiovascular conditions and focus on the importance of a general healthy lifestyle, including diet, physical activity, and medication adherence, and does not include CKD specific information. Following the patient’s completion of the general health education video module, the RA will then readminister the General Health Knowledge and Intent survey.

The usual hospital care control group (and the computerized adaptive education intervention group) will complete the “What’s Next” form, to assess the patient’s commitment to 3 participant-selected self-care activities. Participants also will be contacted 30 days after discharge to complete the follow-up survey.

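### Participants are called blinded, but only the group label is withheld, and staff who know the allocation collect outcomes that include self-ratings

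*Protocol article*

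**What the plan says.** The Blinding section of the protocol article opens with "Trial participants will be blinded after group assignment". It then gives the means: "Participants will view the survey as a Google Form and will not be informed whether they are part of the intervention or control group", and "They will also receive a study packet, which will not identify if they are part of the intervention or control group". It closes by disclosing that "The research team will not be blinded".

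The two arms are described elsewhere in Methods:

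- **Intervention Group:** an avatar presents kidney-disease content, tailored to the patient's prior knowledge, diabetes status and motivation, while an RA advances the modules. "The interactive CKD video can be completed in 30-45 minutes".
- **Trial Design, on the control arm:** "Participants in the control group will receive printed patient education materials informing them of the importance of a general healthy lifestyle". The section adds that this material is meant for cardiovascular patients and contains nothing on CKD.
- **Control Group:** the same printed material is described, but the posttest is then said to follow "completion of the general health education video module, the RA will then readminister the General Health Knowledge and Intent survey".

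On who collects the data, the Randomization section has the RA carry out randomization, assignment and enrollment. The Intervention Group and Control Group sections have the RA conduct the pretest and give the survey again afterwards. At 30 days, "both groups will complete a follow-up call with the project RA".

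**The concern.** Leaving the group name off a form is not the same as masking a participant. A patient who has just finished a narrated kidney module, or has just been given lifestyle material that never mentions kidneys, knows which of these happened. That patient is then asked about CKD. The second safeguard, a masked assessor, is not described at any of the three time points.

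This matters because of the type of outcome. The Primary Outcome section covers attitudes and behavior as well as knowledge, and its surveys mix multiple-choice items with Likert ratings of agreement, own knowledge and likelihood. The secondary outcomes are motivation and intent, and patients also rate their confidence in reaching their chosen goals. Answers of this kind can shift with what the patient thinks is expected, especially when the person administering the survey knows the arm. If the trial is later reported as participant-blinded, readers will give these results more weight than the procedures justify. The limitations in the Discussion do not mention the issue.

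**Working it through.** The point is mainly one of setting the text against itself. The arithmetic at the end is illustrative.

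**1. What is masked.** The Blinding section lists non-disclosure of the group, a survey shown as a Google Form, and an unlabelled packet. None of these conceals the content of the education.

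**2. What the patient can perceive.**

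| Feature | Intervention | Control |
|---|---|---|
| Content | CKD risk factors, stages, treatment options, lifestyle | General lifestyle, no CKD content |
| Format | Interactive avatar-led video | Print (Trial Design, Control Group), but also a video module (Control Group) |
| Duration | 30-45 minutes | Not given |
| RA role in delivery | Advances the modules | Not described |

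The print-versus-video conflict affects how different the formats look. It does not affect the content row. Even if both arms watched a video, only one video would be about CKD, which is what the primary survey tests.

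**3. Who knows the allocation when data are collected.** Under Randomization, the RA consults the spreadsheet before approaching the patient with that arm's packet. The RA's role therefore carries knowledge of the arm at pretest and posttest. The 30-day call is made by a project RA from a team stated to be unblinded, and nothing says that this caller is kept from the allocation.

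**4. Which outcomes are exposed.** Right-or-wrong multiple-choice items are the least exposed. Likert ratings of own knowledge, intent and confidence are the most exposed.

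**5. Scale, on an assumed bias.** Inputs from Statistical Methods: 77 per group, SD 21%, target difference 10%, one-sided type-1 error 5%.

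- *The plan's own figure.* For 90% power, the normal approximation gives 76 per group. The noncentral t gives 77, with power 90.3% at 77. The stated 77 is reproduced under its stated one-sided 5% error.
- *Standard error of the difference:* 21 × √(2/77) = 3.38 points.
- *False-positive rate with no true effect and a differential bias of b points:* Φ(b/3.38 − 1.645).

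| Assumed b (points) | Share of the 10-point target | One-sided false-positive rate |
|---|---|---|
| 0 | 0% | 5% |
| 1 | 10% | 9% |
| 2 | 20% | 15% |
| 3 | 30% | 22% |
| 5 | 50% | 43% |

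The document gives no value for b, so the table shows sensitivity only. It also uses the percent score behind the sample size. It applies only so far as the analysed score contains items that can be shifted by reporting.

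**The case against.** The other side has several good points.

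- **The protocol is open about what it does.** It says what participants are not told and states plainly that the team is unblinded. A reader might infer that it offers blinding as protection against reporting bias. It makes no such claim.
- **Perceiving one's materials is not the same as knowing which arm is experimental.** Both arms have a pretest, education, a posttest, a goal-setting form and a 30-day contact. What patients are told about the other arm is in the consent form, which is not shown. A reader might conclude that allocation is unmistakable to every patient. The document does not establish that.
- **The RA is not the educator.** The avatar presents the content and the RA is barred from offering CKD information. An argument about pleasing one's teacher therefore does not fit. What remains is the presence of an RA who knows the arm.
- **The survey mode is unclear.** Participants view a Google Form and write in the packet, yet the RA is also said to conduct and readminister the survey. The posttest may already be largely self-completed.
- **Full masking of an educational intervention is rarely possible**, and 96 patients had already completed both surveys by December 2024.

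These points limit the claim but do not remove it. The statement that participants are blinded is still not supported by the procedures offered for it, and self-rated items are still gathered by staff who are not masked. An unseen analysis plan could not make the two arms indistinguishable.

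**Conclusion.** The participant-blinding claim is not supported as described. The procedures withhold a label. The arms differ in subject matter whichever control format is correct, so patients can readily perceive what they received. RAs from an unblinded team administer the pretest, the posttest and the 30-day call, on outcomes that include Likert, intent and confidence ratings.

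The size of any resulting bias cannot be estimated from the document, and there is no evidence that bias has occurred. The 9% to 43% range rests on assumed biases of 1 to 5 points, the plan's SD of 21% and 77 per group. A reader might infer that the trial has no protection at all or that its knowledge result is invalid. Neither follows, because right-or-wrong items are much less exposed and some responses may be self-completed. The consequence is narrower: the trial should not be reported as participant-blinded, and self-rated and intent results need a caution.

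**What to change.** 1. **Blinding section:** replace the claim with a statement that participants are not told their group label and that participants and staff are not effectively masked. Do not report the trial as participant-blinded.
2. **Trial Design and Control Group sections:** reconcile whether control participants receive print, a video module or both. State how the posttest is completed in practice. No change of posttest mode is proposed mid-trial.
3. **30-day call:** use a fixed script. Where more than one existing RA is available, have the call made by one who did not run that patient's session and cannot see the allocation. Both arms complete the goal form, so the caller needs no allocation information to ask about progress. A patient may still reveal the arm in conversation.
4. **Reporting:** present right-or-wrong knowledge items separately from self-rated and intent items, and label the latter as open to reporting bias. The primary outcome need not be redefined. Classify the items before any data are analysed. The article says that no analysis has occurred.

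**Cost:** wording changes, minor rota work and a protocol modification report to the IRB. The number of RAs is not given, though Trial Design refers to them in the plural. The masked call would apply only to the remaining follow-ups. At December 2024 the planned 170 less the 96 with both surveys left 74, and the number of 30-day calls already made is not stated. Record the date of change so that calls before and after it can be told apart.
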